### Objectives and Sample Size

2.1

This randomized controlled trial with 6 groups of therapists, assessors, and participants will be conducted from April 2024 to April 2025 in the Department of Rehabilitation Medicine at the Affiliated People's Hospital of Hangzhou Medical College. The study involves a 4‐week intervention for the enrolled patients. The study protocol was approved by the Institutional Review Board of the Affiliated People's Hospital of Hangzhou Medical College and was registered at https://register/clinicaltrials.gov(NCT06313866). Voluntary written informed consent will be obtained from all participants before entering the trial. We reported the trial according to the Consolidated Standards of Reporting Trials (CONSORT) statement (Figure 1).

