### Randomization and Blinding

2.4

Using a random number table method, the PSCI participants in the trial will be randomly allocated to (1) the control group, (2) the EA group, (3) the HOT group, (4) the combination group, (5) the sham group, and (6) the healthy group, with 35 individuals in each group. Notably, the present study was designed as a separate cohort of healthy subjects to assess brain functional abnormalities in patients with PSCI using functional magnetic resonance imaging (fMRI) and to validate the effects of interventions such as acupuncture and ATR volatile oil therapy on brain function. Data from healthy people provide a baseline of normal brain function for the study, helping to identify pathological changes in stroke patients. The allocation process is concealed, and the assessors will be kept blinded to the participant's allocation. Participants are instructed not to discuss their research participation or experiences with the assessors during the evaluation period. Patients will be informed that they would receive either EA treatment, HOT, or both, without being informed about the number of acupoints or the specific stimulation sites.

Acupuncture and herbal treatments will be administered by licensed acupuncturists, while a qualified rehabilitation physician will train a research assessor to evaluate the efficacy of acupuncture. The research assessor and data analysts will remain blinded to group assignment, although participants will be informed during the informed consent process.

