#### Control Group

2.6.1

Given that a considerable proportion of patients will require targeted treatment for underlying conditions such as hypertension, glycemic control, anticoagulation, and lipid regulation, concomitant therapies will be permitted during the study period. Moreover, each patient also underwent cognitive rehabilitation training five days a week with two days of rest for a total of 4 weeks. The standard drug treatment group was the control group. The enrolled patients will receive 5 mg of donepezil hydrochloride per night initially, which is increased to 10 mg per night after 30 days in the absence of any adverse reactions. The total treatment duration is 4 weeks.

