#### Sham Group

2.6.6

In the sham stimulation group, non‐penetrating acupuncture will make the patients experience a feeling similar to acupuncture. But it doesn't pierce the skin. Other treatments will be the same as Section 2.6.5.

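### Section 2.4 has patients told they will receive EA, HOT or both, which is untrue for the control arm (35 of 175 patients) and does not describe the sham arm

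*Protocol article*

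**What the plan says.** Section 2.4 of the protocol article (Randomization and Blinding) lists control, EA, HOT, combination, sham and healthy groups, "with 35 individuals in each group". It then says that "the present study was designed as a separate cohort of healthy subjects", so five groups consist of patients. On what patients are told, the section makes two statements:

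- In the first paragraph: "Patients will be informed that they would receive either EA treatment, HOT, or both". The number of acupoints and the stimulation sites are withheld.
- In the second paragraph, after saying that the assessor and analysts stay blinded to group assignment: "although participants will be informed during the informed consent process".

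The arms that bear on this are described elsewhere:

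- **Control, Section 2.6.1:** "The standard drug treatment group was the control group". These patients receive a named study drug and cognitive rehabilitation training. Neither EA nor HOT is listed for them.
- **Sham, Section 2.6.6:** the non-penetrating "acupuncture will make the patients experience a feeling similar to acupuncture". For the rest of the sham treatment the reader is sent to Section 2.6.5 (the healthy group). That section opens with an olfactory treatment and then refers back to Section 2.6.1.
- **Discussion, limitations paragraph:** the absence of a sham group is given as a limitation of the design.

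Section 2.1 adds: "Voluntary written informed consent will be obtained from all participants before entering the trial".

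**The concern.** The statement in Section 2.4 offers three possibilities, but a patient can be allocated to any of five arms. Someone who agrees on that basis could be assigned to a study drug without EA or HOT, or to a needle that does not enter the skin. Neither was among the options named.

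Two things are at stake. The first is the accuracy of what patients are told before they consent. This population is selected for cognitive impairment, and a family member may sign (Section 2.2). The second is the comparator. A control patient told to expect EA, HOT or both would see at once that neither had come. That could prompt withdrawal or treatment outside the trial in one arm more than in the others.

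**Working it through.** **Step 1. Group sizes.** Sections 2.1 and 2.4 give six groups of 35: 6 × 35 = 210, which matches the stated total. Leaving out the separate healthy cohort gives 5 × 35 = 175 patients.

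**Step 2. Compare the statement with each patient arm.**

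| Arm | Treatment described | Is it true that the patient receives EA, HOT or both? |
|---|---|---|
| EA (2.6.2) | EA | Yes |
| HOT (2.6.3) | HOT | Yes |
| Combination (2.6.4) | EA and HOT | Yes |
| Control (2.6.1) | Standard drug and cognitive training | No |
| Sham (2.6.6) | Needling without penetration; the rest as in 2.6.5 | Undetermined; the needling is not described in either case |

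**Step 3. Follow the sham cross-reference.** Section 2.6.6 leads to 2.6.5. Its first sentence gives an olfactory treatment in nearly the words that open the HOT section. Its last sentence says the procedure is that of 2.6.1, the control section, which has no olfactory treatment. If the first sentence governs, sham patients receive HOT and the statement is true of them as to HOT. If the last governs, they receive neither EA nor HOT and it is untrue. The text does not settle which.

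**Step 4. Share of patients for whom the statement is untrue.** Share = patients in the affected arms ÷ patients randomised.

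| Affected arms | Of 175 patients (five arms) | Of 210 (if all six groups are counted) |
|---|---|---|
| Control only | 35/175 = 20.0% | 35/210 = 16.7% |
| Control and sham | 70/175 = 40.0% | 70/210 = 33.3% |

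The 175 denominator is the relevant one, because the statement is addressed to patients and the healthy group is called a separate cohort.

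**Step 5. Set the two statements in Section 2.4 side by side.** In context, the second concerns knowledge of group assignment. If it means that patients learn their own group at consent, it conflicts with telling all of them to expect EA, HOT or both, and a sham needle meant to feel like acupuncture loses its purpose. If it means only that patients receive study information, the only treatment content Section 2.4 gives for that information is the three-option statement. Neither reading makes the first statement true for control patients.

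**The case against.** The strongest reply is that the sentence sits in a section on blinding, and its second half is about withholding the number of acupoints and the sites. It is not offered as the full consent text. The consent form is not shown, an article condenses such material, the review board approved the protocol, and the same section says participants will be informed during consent. The form may well describe all five arms.

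Much of this stands. A reader might infer that control patients are never told of the drug arm, or that their consent is uninformed. The documents do not support that, because they do not show what the form says. The reply does not rescue the sentence itself. It is a positive statement of what patients will be told, it is untrue for control, and staff working from the protocol could follow it.

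A reader might also infer a flat 40%. That requires sham patients to receive no olfactory treatment, which the cross-reference leaves open.

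Finally, a reader might infer that the control arm will lose more patients than the 10% dropout planned in Section 2.1, or will seek treatment outside the trial. This is possible, but no figure in the article supports a size for it. Controls do receive active care, and disappointment can arise in any visibly different comparator arm even with full disclosure.

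**Conclusion.** The concern holds as an error in the text. The statement in Section 2.4 is untrue for the control arm: 35 of 175 patients, 20%. It does not describe the sham needling on any reading. If sham patients receive no olfactory treatment, it is untrue for 70 of 175, 40%. It also conflicts with the paragraph that follows it.

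These figures assume equal arms of 35 as planned and a healthy group outside the patient randomisation. The conclusion concerns the protocol text only. Whether patients were in fact misinformed depends on a consent form that is not shown, and any effect on dropout or outside treatment is not quantified.

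**What to change.** - **Replace the sentence in Section 2.4.** Every patient should be told before consent that allocation is by chance among all the patient arms: standard drug treatment, EA, HOT, both, or a needling procedure that may be inactive. The number of acupoints and the stimulation sites can still be withheld.
- **State whether patients learn their own group,** and bring the second paragraph of Section 2.4 into line with the answer.
- **Reconcile the arm descriptions.** Sections 2.6.1, 2.6.5 and 2.6.6 should make clear whether sham patients receive olfactory treatment. The limitation in the Discussion that there is no sham group must be reconciled with Sections 2.4 and 2.6.6. The patient information should then match the result.
- **Check the consent form against the new wording.** If it already covers all five arms, only the protocol text needs correcting.
- **Optional:** ask all patient arms at weeks 4 and 8 about acupuncture or aromatic oil used outside the trial, so that any imbalance can be seen.

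The cost is a text correction and, if the form has the same fault, a consent amendment with ethics approval. A few patients may decline once told of the control and sham possibilities.

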### Allocation Concealment

2.5

#### Generation of Random Allocation Sequence

2.5.1

Use of randomization tools: A random number table or equivalent randomization tool was employed to generate a numerical randomization sequence.Group assignment: Each random number was uniquely mapped to a participant ID and subsequently designated as either the experimental group or control group. This process was exclusively conducted and documented by authorized personnel.

#### Preparation and Preservation of Random Allocation Table

2.5.2

Table creation: A formal “Random Allocation Table” was created to systematically record grouping information. The table was prepared in triplicate to ensure data integrity and redundancy.Secure storage: The random allocation table was strictly preserved using multiple security measures, including encrypted digital storage and physical safeguards (e.g., locked cabinets), to prevent unauthorized access.

#### Implementation of Allocation Concealment

2.5.3

Opaque sealed envelopes/containers: The allocation information was sealed in sequentially numbered, opaque envelopes to prevent premature disclosure of group assignments.Custodian protocol: Three key stakeholders the principal investigator, acupuncture therapists, and statisticians—were each entrusted with separate copies of the allocation table. Simultaneous authorization from all custodians was required for any disclosure.

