#### Unblinding and Verification Procedures

2.5.4

Unblinding protocol: Group allocation information was only revealed through the synchronized opening of all sealed copies of the allocation table, ensuring temporal alignment and procedural transparency.Allocation validation: Actual group assignments were systematically cross‐verified against the original randomization records through independent auditing, confirming compliance with the predetermined allocation scheme.

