### Data Security and Monitoring

2.8

The data management of this study is overseen by the research team to uphold the authenticity, integrity, confidentiality, and traceability of clinical trial data. The Case Report Form (CRF) will be completed by the principal investigator or other authorized researchers, with only qualified medical researchers permitted to input raw clinical assessment/safety data. Any modifications made to the raw data on the CRF by the principal investigator or other authorized researchers will be recorded. Approved data modifications necessitate the researcher making the changes by signing their name, indicating the modification date, and providing the rationale for the modification. Researchers will adhere to standard operating procedures to ensure quality control of the clinical trial and the implementation of a quality assurance system. All observed results and findings in the clinical trial will be validated to guarantee the data's reliability and to ensure that all conclusions drawn from the clinical trial are based on original data. Quality control measures will be enforced throughout the data processing stages to verify the reliability and accuracy of all processed data.

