### Data Analysis

2.11

Researchers who are blind to the groupings will conduct data management and statistical analysis on the data acquired using the statistical software SPSS 22.0 (SPSS Inc., Chicago, IL, United States). Descriptive statistics will be utilized to depict the baseline characteristics of the two participant groups, with mean ± standard deviation for normally distributed continuous data and median and quartiles for non‐normally distributed continuous data. The normality of the data will be assessed using the Shapiro–Wilk test, and the homogeneity of variance will be assessed using the Levene test. One‐way analysis of variance (ANOVA) will be used for comparisons among multiple groups for normally distributed continuous data, while repeated measures analysis of variance will be used for within‐group pre‐ and post‐treatment comparisons. The Kruskal–Wallis test will be employed for non‐normally distributed continuous data. The significance level (α) for the statistical hypothesis tests will be set at *p* < 0.05, one‐tailed.

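### Allocation concealment and blinding are described contradictorily and are not secured: table custody, the disclosure rule and what participants are told cannot all stand as written

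*Protocol article*

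**What the plan says.** **Custody.** Section 2.5.2 describes one formal allocation table: "The table was prepared in triplicate to ensure data integrity and redundancy". Under Section 2.5.3 the principal investigator, the acupuncture therapists and the statisticians "were each entrusted with separate copies of the allocation table", and "Simultaneous authorization from all custodians was required for any disclosure". The same section puts the allocation information in opaque, sealed envelopes numbered in sequence. Section 2.5.2 adds encrypted and locked storage.

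**Disclosure.** Section 2.5.4, headed as unblinding and verification, states: "Group allocation information was only revealed through the synchronized opening of all sealed copies of the allocation table".

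**Blinding of staff.** Section 2.4 says that the research assessor and the data analysts stay blinded. Section 2.11 repeats this for the analysis: "Researchers who are blind to the groupings will conduct data management and statistical analysis". Section 2.8 says: "The Case Report Form (CRF) will be completed by the principal investigator or other authorized researchers".

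**What participants are told.** Section 2.4 makes two statements. The first is "Patients will be informed that they would receive either EA treatment, HOT, or both", with the number of acupoints and the stimulation sites withheld. The second follows the sentence on assessor and analyst blinding to group assignment: "although participants will be informed during the informed consent process". Section 2.1 places consent before entry to the trial.

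**The concern.** The copies of the full list sit with the people best placed to act on it: those who lead the trial, those who give the needling, and statistical staff. The only stated way to learn an assignment is to open every copy at once. Therapists cannot treat without knowing the arm, so the text either exposes the whole list early or relies on a route that its own rule excludes.

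The stakes are the usual ones. Foreknowledge of the next assignment permits selective enrolment. An analyst who knows the groups can steer analysis choices. A sham that patients recognise no longer controls for expectation, which is the reason for making it feel like acupuncture (Section 2.6.6). None of this can be repaired in the analysis afterwards.

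**Working it through.** No planned figure rests on this point, so the check sets the statements side by side.

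**1. Inputs.** Three copies of the table (2.5.2); three custodian roles (2.5.3); 35 people per group and five patient arms, leaving out the healthy cohort (2.4). Patients with an assignment to protect: 5 × 35 = 175.

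**2. Who must know, and when.** The therapist must know the arm by each patient's first session. Each patient therefore needs a disclosure during recruitment.

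**3. Two readings of the disclosure rule.**
- *Literal.* Group information is revealed only by opening all copies of the table. The first treated patient then triggers the opening, and up to 175 − 1 = 174 later assignments become known to the principal investigator, the therapists and the statisticians. The envelopes serve no purpose.
- *Envelopes as the working route.* Each assignment comes from the next envelope, and the table stays sealed until final unblinding or audit. Concealment and analyst blinding can then survive. But the word only in 2.5.4 is wrong, and the joint authorization that 2.5.3 requires for any disclosure does not describe how envelopes are opened.

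On either reading at least one sentence must change.

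**4. Analysts and data recording.** Statisticians are custodians in 2.5.3, and analysts are blind in 2.4 and 2.11. No sentence says whether these are the same people, and none keeps the roles apart. The principal investigator is a custodian and may complete the CRF. The assessor is not a listed custodian, so scoring of the MoCA is not directly exposed. The routes at risk are recruitment, data recording, data management and analysis.

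**5. Two readings of what participants are told.**
- *They learn their arm at consent.* This is the natural reading, because the sentence has just spoken of group assignment. Consent precedes entry, so a patient could accept or decline according to arm, and a sham patient would know it is sham.
- *They are told only of EA, HOT or both.* Sham assignment is not revealed, but the statement is inaccurate. Control patients (2.6.1) receive neither. Sham patients (2.6.6) receive needling that does not pierce the skin, which the statement does not cover. The cross-reference from 2.6.6 to 2.6.5, and from there to 2.6.1, leaves unclear whether they also receive an olfactory treatment. Arms affected: 2 of 5, or 2 × 35 = 70 of 175 patients (70/175 = 40%).

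No reading leaves both sentences of 2.4 correct.

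**The case against.** A reader might infer that concealment, analyst blinding and the sham control have all failed. The documents do not support that, for these reasons:

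- The copies are sealed, locked or encrypted, and released only by joint authorization. Holding a sealed copy is not the same as knowing its contents.
- Section 2.5.4 stands under an unblinding heading. It can be read as the end-of-trial procedure, with the envelopes in 2.5.3 doing the assigning. On that reading the first treated patient exposes nothing.
- The custodian statisticians are not shown to be the blinded analysts, and the assessor holds no copy. Completing a CRF is not scoring the MoCA.
- Disclosure of the arm at consent is the natural reading of 2.4 but not the only one. The other sentence does not reveal sham assignment, and sealed envelopes fit poorly with naming the arm before entry.
- The abstract claims assessor blinding only, so participant blinding is not promised across the trial.

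It can also be said that an article condenses its procedures and that Section 2.10 promises SOPs for randomization and blinding.

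The first five points stand, and they limit the finding to contradiction and lack of protection. The last does not remove it, because the difficulty lies in statements that the article does make and that cannot all be followed. Sealing the copies also does not explain why treating therapists need the full list.

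**Conclusion.** The point holds as a contradiction that must be resolved. Sections 2.4, 2.5.3, 2.5.4 and 2.11 do not describe one workable scheme, and neither concealment nor blinding is secured by the text.

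The size of any bias cannot be derived from the document. The figure of up to 174 of 175 assignments is an upper bound that depends wholly on the literal reading of 2.5.4. The 70 of 175 patients for whom the statement on EA, HOT or both does not fit depends on the arm descriptions in 2.6.1 and 2.6.6. For sham patients it assumes that the cross-reference is not meant to give them HOT; even if it is, the statement leaves out the sham needling. Loss of the sham's purpose depends on the natural, but not certain, reading that participants learn their arm at consent.

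**What to change.** 1. **Assignment (2.5.3, 2.5.4).** State that each patient is assigned by opening the next numbered envelope after consent and baseline assessment. Limit 2.5.4 to unblinding at the end of the trial or in an emergency.
2. **Custody (2.5.3).** Withdraw the copies from the principal investigator, therapists and statisticians. Place the full table with a custodian who has no part in recruitment, treatment, assessment or analysis.
3. **Analysis (2.4, 2.11).** Give analysts coded arm labels until the primary analysis is done.
4. **Participant information (2.4).** Replace the two sentences with one: consent lists all possible arms, including control and sham, without naming the assigned arm, and patients who are needled are not told whether the needling is real or sham.
5. **If allocation has already taken place.** Sections 2.5.1 to 2.5.4 are in the past tense and 2.1 dates the trial April 2024 to April 2025, so this may apply. Report the procedure actually used, including who held and opened what and what participants were told, and limit the blinding claims to match.

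The cost is small: changes to SOP and consent wording, and re-housing the list. An uninvolved custodian has to be found, and the document names none. No change to treatments, assessments or sample size is needed.
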